### Participant timeline {13}

The total study duration for each participating dyad is 13 weeks. After informed consent is obtained, the mother and child are asked to participate in the pre-test, during which the mother is asked to fill out several questionnaires and 10 min of parent-child interactions are videotaped. In addition, we ask a social worker in the domestic violence shelter to fill out a questionnaire about the child. Prior to the pre-test, the dyad is allocated to NIKA or the waitlist usual care group (the dyad will be notified about this directly after the pre-test). NIKA consists of one intake and four 1-h sessions, divided over 5 weeks. During this time, dyads in the waitlist group only receive CAU in the domestic violence shelter. In week 7, a post-test is conducted, which is similar to the pre-test. Phase 2 of the design starts in that same week. Mothers who report clinical PTSD symptoms at the post-test are allocated to EMDR or the waitlist usual care group. EMDR consists of one intake and a maximum of five 90-min sessions over the course of 5 weeks. Mothers in the waitlist group only receive CAU during this period. Mothers who do not report clinical PTSD symptoms in phase 2 are not included in the randomization. They will still be involved in the post-test of phase 2, to prevent dropout bias (i.e., by making sure the investment for this study will be the same for each participating dyad, it is not likely that dropout rates will differ for the conditions). In week 13, the post-test of phase 2 takes place for all dyads, which is similar to the previous assessments. All assessments take place in the domestic violence shelter or, in case the dyad’s treatment is continued through ambulatory care, at the dyad’s home. The assessments are conducted by two trained (assistant) researchers and take approximately 1 h each. See Fig. 3 for an overview of the timeline for each dyad.

**Fig. 3 Fig3:**
[figure not shown]
Schedule of enrolment, interventions, and assessments

### Sample size {14}

The planned sample size for this study is *N* = 150. Separate power calculations for the two study phases have been conducted.

#### Phase 1

We conducted a power analysis for longitudinal linear mixed effect models with unbalanced designs in R using the “powerlmm” package [76]. Based on recent meta-analyses regarding the effectiveness of trauma-informed parenting interventions after violence exposure [77] and a short-term attachment-based intervention that includes some components similar to NIKA [78], we assumed an effect size of *d* = 0.50 for the effects of NIKA on disrupted and sensitive parenting. We estimated three-level models accounting for repeated measures over time (level 1) and partial nesting of families (level 2) within therapists (level 3) (only in the NIKA group). We estimated approximately 50% variance to occur between subjects and 5% variance between therapists. For a sample of *N* = 150 (*n* = 75 per group), two time points, and two-sided testing with a significance level of *α* = .05, we will have 86% power to detect effects of *d* = 0.50.

#### Phase 2

The estimated effect size of EMDR therapy on PTSD symptoms of the mother is based on a recent meta-analysis in which effect sizes of EMDR therapy were reported within a range of *g* = 0.67–1.18 [79]. Because the current implementation of EMDR therapy (focus on memories of traumatic events that are related to their PTSD symptoms and also hinder positive parent-child interactions) is different from previous studies, we decided to stay on the conservative side of this range by assuming an effect size of *d* = 0.60 for this study. We estimated three-level models accounting for repeated measures over time (level 1) and nesting of mothers (level 2) within the previous condition (NIKA versus waitlist) (level 3). We estimated approximately 50% variance to occur between subjects and 5% variance between previous conditions (NIKA versus waitlist). For a sample of *N* = 80, (*n* = 40 per group), two time points, and two-sided testing with a significance level of *α* = .05, we will have 75% power to detect effects of *d* = 0.60. With a sample of *N* = 150 in phase 1, this would imply that 53% of the mothers who are recruited for this study should report clinical trauma symptoms in order to be included in the randomization for phase 2. We made this estimation based on a recent report which revealed that all women in one of the participating domestic violence shelter locations experienced severe and chronic domestic violence and 75% of the women report traumas of their own childhood [80].

To explore the synergetic effect of NIKA and EMDR therapy, a two-level analysis (only accounting for repeated measures over time, thus not considering nesting of families within therapists), estimating 80% variance to occur between subjects, we will have 68% power to detect effects of *d* = 0.50.

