## Assignment of interventions: allocation

### Sequence generation {16a}

In both phases of the RCT, dyads are randomly assigned to one of the two conditions. Randomization occurs with a random number generator in Microsoft Excel (1:1 allocation), stratified by the participating domestic violence shelter locations and using permuted blocks. The first randomization (NIKA versus waitlist CAU) is done prior to the pre-test by a researcher who will not conduct the pre-test. The second randomization (EMDR therapy versus waitlist CAU) is done after post-test 1. Only mothers who report clinical PTSD symptoms on the PCL-5 (for a more detailed description of this questionnaire and the cut-off score that is used, see the “Outcomes {12}” section) are randomized, according to a similar procedure in Microsoft Excel.

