## Statistical methods

### Statistical methods for primary and secondary outcomes {20a}

We will conduct the analyses for this study through three-level linear mixed effect models in R (nlme, lmr, and mitml packages) that account for repeated measures over time (level 1) and nesting of dyads (level 2) within therapists (level 3). More details on the analyses are described earlier in this protocol under the “Outcomes {12}” and “Sample size {14}” sections.

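### The phase 2 model for the EMDR effect on PCL-5 has two conflicting third levels, and one of them treats the two-value phase 1 allocation as a random cluster

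*Protocol article*

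**What the plan says.** Three parts of the protocol article bear on the phase 2 model.

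- **Sample size {14}, Phase 2.** The third level is given as "nesting of mothers (level 2) within the previous condition (NIKA versus waitlist) (level 3"), with "50% variance to occur between subjects and 5% variance between previous conditions (NIKA versus waitlist"). No therapist term appears. The calculation is "For a sample of *N* = 80, (*n* = 40 per group), two time points", and the result is "two-sided testing with a significance level of *α* = .05, we will have 75% power to detect effects of *d* = 0.60".
- **Statistical methods {20a}.** The analyses are three-level mixed models that "account for repeated measures over time (level 1) and nesting of dyads (level 2) within therapists (level 3"). Previous condition is not mentioned and phase 2 has no model of its own. The section points to Outcomes {12} and Sample size {14} for further detail.
- **Outcomes {12}.** The PCL-5 contrast is the change from the first to the second post-test, EMDR versus waitlist. Here too the reader is sent to Sample size {14} for the analysis.

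For comparison, the Phase 1 part of Sample size {14} uses partial nesting: families sit within therapists in the NIKA arm only, with 5% of variance between therapists. The section on adherence {11c} shows that EMDR is delivered by more than one therapist but does not say how many.

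**The concern.** Because both {12} and {20a} refer to the Sample size section for analysis detail, its phase 2 description cannot be read as power planning only. Two analysts following the article could fit different models, with different standard errors, to a primary outcome.

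Each version also has its own defect. In the Sample size version, phase 1 allocation is a random level although it is a randomised factor with two known values, not a sample from a population of clusters. In the {20a} version, phase 1 allocation is absent, and dyads are described as fully nested in therapists although waitlist mothers have no EMDR therapist. No version contains both phase 1 arm and therapist nesting limited to the EMDR arm.

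At stake are the reproducibility of the EMDR analysis and, if mothers treated by the same therapist respond alike, the honesty of its standard error.

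**Working it through.** **Inputs from Sample size {14}, Phase 2:** 40 mothers per arm, d = 0.60, two-sided α = .05, two time points, 50% of variance between subjects, 5% between previous conditions.

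**1. The plan's own figure.** Take total variance as 1 and residual share as 0.50.
- Variance of a change score: 2 × 0.50 = 1.0.
- Variance of the arm difference in change: 1.0 × (1/40 + 1/40) = 0.05.
- Standardised effect: 0.60/√0.05 = 2.683.
- Power: Φ(2.683 − 1.96) = 76.5%; noncentral t on 78 df, 75.5%. The stated value is 75%.

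With a residual share of 0.45 or 0.55 the t result is 79.8% or 71.5%, so neither matches. The 5% level-3 share must lie within the 50% as a random intercept, where it cancels from the change contrast.

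**2. What two units can tell about a variance.** Average the two time points per mother. The within-condition variance is 0.45 + 0.50/2 = 0.70, so each condition mean of 40 mothers has sampling variance 0.70/40 = 0.0175. With a true level-3 variance of 0.05, the moment estimate is zero or negative when a χ² on 1 df falls below 0.0175/(0.05 + 0.0175) = 0.259, which has probability 0.39. Simulation also gave 39%, with a 5th–95th percentile range of 0 to 0.24 around the true 0.05. With one observation per mother the cut-off is 0.95/(0.95 + 40 × 0.05) = 0.322 and the probability 0.43. So the estimate is zero in about 40% of trials.

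**3. Phase 1 arm as a fixed effect.** Adding the arm and its time interaction leaves 76 df. The noncentral t gives 75.5%, unchanged.

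**4. Therapist variance in EMDR response.** The protocol gives neither the number of EMDR therapists (k) nor their variance share (s). Assume k = 4 to 10 and s = 2% or 5%, with the variance added to the post-test in the EMDR arm only:

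V = 2/40 + s/k

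Type I error if ignored = 2 × [1 − Φ(1.96 × √(0.05/V))]

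Power if modelled = Φ(0.60/√V − 1.96)

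| s | k | V | Type I error if ignored | Power if modelled, normal | Power if modelled, t |
|---|---|---|---|---|---|
| 2% | 4 | 0.0550 | 6.2% | 73% | 63% |
| 2% | 10 | 0.0520 | 5.5% | 75% | 72% |
| 5% | 4 | 0.0625 | 8.0% | 67% | 56% |
| 5% | 10 | 0.0550 | 6.2% | 73% | 69% |

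The last column uses a noncentral t with Satterthwaite df = V²/[a²/(k − 1) + b²/39], where a = 1/40 + s/k and b = 1/40. Simulation at s = 5% gave type I error of 7.7%, 7.0% and 6.1% for 4, 5 and 8 therapists.

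**5. Is 5% in this form the protocol's own assumption?** Put it on the NIKA-arm post-test in phase 1 (75 per arm, d = 0.50): V = 2/75 + 0.05/k. Power is Φ(0.50/√V − 1.96) = 71% for k = 4 and 80% for k = 10, against the stated 86%. Without the term, phase 1 gives 86.0% (t). The stated phase 1 figure therefore does not carry therapist variance in this form, and step 4 is an added assumption.

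**The case against.** The strongest reply is that {20a} is the statistical methods section and names therapists as the third level. If it governs, therapist clustering is modelled in phase 2, and the inflated type I error does not arise. That stands: the inflation follows only if the Sample size description overrides {20a}. It does not remove the inconsistency, since {20a} itself defers to the Sample size section, and full nesting in therapists still does not fit an arm without an EMDR therapist.

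Second, the two-unit variance is a nuisance parameter. A stable phase 1 difference cancels in the change score and EMDR is randomised, so the EMDR estimate is not biased. That also stands; on phase 1 arm the point is about correct specification, not bias or lost power.

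Third, coding details may be left to a fuller document. That would excuse silence, but not two conflicting statements.

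A reader might also infer that the second randomisation is deficient because it is "stratified by the participating domestic violence shelter locations and using permuted blocks" without phase 1 arm as a stratum. The document does not support that. The randomisation is valid as it is. A 16:24 EMDR split among an assumed 40 NIKA mothers would lower power for the exploratory synergy comparison from 68.3% to only 66.5%. Crossing arm with shelter during recruitment would risk sparse blocks and could need ethics approval.

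**Conclusion.** The inconsistency is real and concerns a primary hypothesis: the third level is previous condition in one section and therapists in the other. Using a two-value randomised factor as a random level is a specification error, since its variance would be estimated as zero in about 40% of trials at the plan's own 5% share.

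It is tempting to conclude that the 75% is wrong or that the trial will run at an inflated error rate. Neither follows. The 75% reproduces. The range of 5.5–8% for type I error requires that therapist variance goes unmodelled, and it rests, like the 67–75% for power (about 56–72% with small-sample df), on assumed values of 4–10 therapists and a 2–5% share placed on the EMDR-arm post-test. The point should be corrected before the phase 2 data are analysed, but it does not undermine the design.

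**What to change.** - Make Sample size {14} and Statistical methods {20a} state the same phase 2 model.
- Enter phase 1 allocation and its interaction with time as fixed effects, in place of the random third level.
- Add a random effect for EMDR therapist on the response in the EMDR arm only, parallel to the partial nesting already used for NIKA in phase 1.
- Restate phase 2 power with the number of EMDR therapists and the assumed variance share given, and use small-sample degrees of freedom.

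The cost is a few lines of text and two degrees of freedom (78 to 76). The fixed effects leave power at about 75%. The restated figure will be lower to the extent that therapist variance is assumed. The randomisation list needs no change.

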**Methods:**

This study uses a multicenter randomized controlled design across multiple domestic violence shelters in the Netherlands. We aim to recruit 150 parent-child dyads with children aged between 0.5 and 6 years old. The study design consists of two phases. During the first phase for testing the effect of NIKA only, eligible dyads are randomly allocated to either NIKA or a waitlist usual care group. A pre-test is conducted prior to the treatment period and a post-test takes place directly afterwards (6 weeks after the pre-test). Phase 2 follows directly for testing the effects of EMDR and the combination of NIKA and EMDR. Parents who report clinical PTSD symptoms are randomly allocated to either EMDR therapy or a waitlist usual care group. Parents who do not report clinical PTSD symptoms only receive care as usual. Six weeks later, a post-test of phase 2 is conducted for all participating dyads. Primary study outcomes are disrupted parenting behavior, sensitive parenting behavior, and parental PTSD symptoms. Secondary study outcomes include PTSD symptoms and behavioral and emotional problems of the child.

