### Methods in analysis to handle protocol non-adherence and any statistical methods to handle missing data {20c}

We will conduct multilevel multiple imputation [81, 82] to be able to include all dyads, including families who dropped out throughout the project, in the analyses (intention to treat).

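### The 86% and 75% powers are complete-data figures on every dyad recruited, and the 53% that feeds Phase 2 rests on trauma exposure, not on a PCL-5 rate

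*Protocol article*

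**What the plan says.** The abstract sets the recruitment target: "We aim to recruit 150 parent-child dyads with children aged between 0.5 and 6 years old". *Sample size {14}*, Phase 1, uses the same number as the analysed sample: "For a sample of *N* = 150 (*n* = 75 per group), two time points, and two-sided testing". It assumes d = 0.50 "for the effects of NIKA on disrupted and sensitive parenting", with about 50% of variance between subjects and 5% between therapists, and concludes "we will have 86% power to detect effects of" that size.

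Phase 2 assumes d = 0.60, 40 mothers per group and about 50% between-subject variance, and states 75% power. The 80 mothers are then expressed as a share of those recruited: "this would imply that 53% of the mothers who are recruited for this study should report clinical trauma symptoms". The support offered is a report from one participating location in which all women had experienced severe, chronic violence and "75% of the women report traumas of their own childhood".

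Entry to Phase 2 is defined differently. Under *EMDR therapy*, a mother is randomised only if her PCL-5 score is 31 or more at post-test 1.

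Section {20c} plans multilevel multiple imputation so that all dyads are analysed, "including families who dropped out throughout the project". No retention rate is given, and 150 serves both as the number recruited and the number analysed.

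**The concern.** There are two weaknesses, and both bear on primary hypotheses.

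**Loss.** A power computed on everyone recruited is reached only if everyone supplies the outcome. Section {20c} provides for dropout. Multiple imputation keeps a dyad in the intention-to-treat set, but an unobserved post-test adds little information beyond what other variables predict. Precision therefore stays close to that of the observed dyads. Phase 2 is exposed twice: mothers lost before post-test 1 cannot be screened for it, and mothers lost afterwards have no Phase 2 outcome.

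**The 53%.** It is 80/150 worked backwards, so it states what is needed. The evidence offered for it concerns exposure to trauma. Exposure does not give the share of mothers above a symptom cut-off, here measured after six weeks and after half the sample was allocated to NIKA.

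The stake is interpretation. The EMDR comparison starts at 75%, so a null result read against that figure could be given more weight than the data carry.

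**Working it through.** **Inputs from *Sample size {14}*.** Phase 1: 75 per group, d = 0.50. Phase 2: 40 per group, d = 0.60. Two time points, "two-sided testing with a significance level of" 0.05, 50% between-subject variance. **Assumed, because the protocol gives none:** loss of 10, 15 or 20%, and shares scoring 31 or more between 40% and 75%.

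**Step 1: reproduce the stated powers.** With total variance 1 and half of it between subjects, the SD of change is √(2 × 0.50) = 1, so d carries over unchanged. The noncentrality is d/√(2/n), referred to a noncentral t with 2n − 2 degrees of freedom.
- Phase 1: 0.50/√(2/75) = 3.062, 148 df, power 86.0% (stated 86%).
- Phase 2: 0.60/√(2/40) = 2.683, 78 df, power 75.5% (stated 75%).

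Both match without any allowance for loss.

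**Step 2: apply loss L.** Put n(1 − L) in place of n. The last column is 80/[150(1− L)], the share of mothers still present at post-test 1 who must score 31 or more to supply 80.

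| Loss | Phase 1 n per group | Phase 1 power | Phase 2 n per group (80 randomised) | Phase 2 power | Share needed for 80 |
|---|---|---|---|---|---|
| 0% | 75 | 86% | 40 | 75% | 53% |
| 10% | 67.5 | 82% | 36 | 71% | 59% |
| 15% | 63.75 | 80% | 34 | 68% | 63% |
| 20% | 60 | 78% | 32 | 66% | 67% |

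**Step 3: vary the share.** Phase 2 N = 150 × retention × share. At 85% retention:

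| Share scoring 31 or more | N | Power at d = 0.60 |
|---|---|---|
| 40% | 150 × 0.85 × 0.40 = 51 | 56% |
| 53.3% | 150 × 0.85 × 0.533 = 68 | 68% |
| 65% | 150 × 0.85 × 0.65 ≈ 83 | 77% |
| 75% | 150 × 0.85 × 0.75 ≈ 96 | 83% |

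**Step 4: adjust for baseline.** A 50% between-subject share implies a pre-post correlation of 0.5. Adjusting the post-test for its baseline leaves residual variance 1 − 0.5² = 0.75, against 1 for the change score. At 15% loss:
- Phase 1: 0.50/√(0.75 × 2/63.75) = 3.260, power 90%.
- Phase 2 (N = 68): 0.60/√(0.75 × 2/34) = 2.857, power 80%.

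At 20% loss the same formula gives 88% and 78%. None of these includes therapist variance in change.

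**The case against.** **The stated powers are correct for their stated N.** This stands. 86%, 75% and 53% all reproduce, so there is no arithmetic error. What is missing is any margin.

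**Retention is well provided for.** This also stands. Leaving the shelter is not dropout: sessions and assessments continue at home, dyads who move are visited, mothers are paid after each assessment, and assessments are sought even when treatment is refused. That is a case for low loss, not zero loss, and section {20c} does not assume zero.

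**A condensed article may leave detail to the full protocol.** That would excuse an omitted derivation. Here the article itself states the N, the powers and the basis for the 53%, and these can be judged as written.

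Three stronger readings may tempt a reader, and the document supports none of them:
- *The therapist effect was ignored.* The 86% equals the power for independent dyads when residual variance is 50%. But the text states partial nesting in the NIKA arm and 5% therapist variance. If the split is 50 + 5 + 45, independent dyads give 89% (change SD √(2 × 0.45) = 0.949). Letting the 5% act on change with about 19 therapists gives 0.50/√(2 × 0.90/75 + 0.05/19) = 3.064, or 86% again. Neither the placement of the 5% nor the number of therapists is given, so the figure cannot settle the matter.
- *The design cannot reach its stated powers.* Step 4 shows that it can, with baseline adjustment, at N = 150. Phase 2 can also do so if the share is well above 53%.
- *The 53% is too high.* Exposure data do not establish it, but nothing in the protocol shows it to be too high either.

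**Conclusion.** The point holds as one about planning assumptions. The 86% and 75% are best-case values for the planned comparison of changes: they require all 150 recruited dyads to be analysed, and 53% of all recruited mothers both to reach post-test 1 and to score 31 or more. At 10 to 20% loss, Phase 1 falls to about 82 to 78%, and Phase 2 to about 71 to 66% with 80 randomised. To supply those 80 after 15 or 20% loss before post-test 1, 63% or 67% of the remaining mothers must meet the cut-off. The 53% has no symptom-based support, and its error could run either way: at 15% loss, shares from 40% to 75% give Phase 2 power from 56% to 83%.

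These sizes rest on assumed loss and shares, on the stated effect sizes and 50% between-subject variance, and on imputation adding little information about unobserved post-tests.

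**What to change.** Keep N = 150 and make three changes in *Sample size {14}* and the statistical methods.

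1. State an expected retention range and give both powers across it, with Phase 2 N written as 150 × retention × share with PCL-5 of 31 or more.
2. Replace the exposure rationale with the share scoring 31 or more among mothers who have reached post-test 1. Pool it over NIKA and waitlist so that no comparison between arms is revealed.
3. Specify, before outcomes are examined by arm, that each comparison adjusts for the value already collected at the start of its phase: the pre-test for Phase 1 and post-test 1 for Phase 2. Under the protocol's variance split this more than offsets 15% loss relative to the stated powers. Two cautions belong beside that claim. Therapist variance in change would lower both figures. In Phase 2 the baseline is restricted to scores of 31 or more, so its correlation with the outcome may be below 0.5 and the 80% may be optimistic.

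The cost is recalculation and wording. The power of the change comparison will look less favourable. No additional dyads or assessments are needed.

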### Methods for additional analyses (e.g., subgroup analyses) {20b}

To explore the synergetic effect of NIKA and EMDR therapy, a two-level analysis (only accounting for repeated measures over time, thus not considering nesting of families within therapists) will be conducted to compare dyads who have received both NIKA and EMDR, to dyads who have only received NIKA. We will compare changes in disrupted parenting behavior, sensitive parenting behavior, child PTSD symptoms, and behavioral and emotional problems from the pre-test to the second post-test between these two groups, see the “Sample size {14}” section for more details about the analysis.

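### The 68% power for NIKA plus EMDR versus NIKA only assumes 80% between-subject variance, but Phase 1 assumes about 50% for the same two parenting outcomes; at 50%, with an inferred 20 per group, power is about 34%

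*Protocol article*

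**What the plan says.** All the power statements are in the protocol article under Sample size {14}.

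- **Phase 1** (NIKA versus waitlist; disrupted and sensitive parenting): 75 per group, d = 0.50, 86% power. The variance assumption is: "We estimated approximately 50% variance to occur between subjects and 5% variance between therapists".
- **Phase 2** (EMDR versus waitlist; maternal PTSD symptoms): 40 per group, d = 0.60, 75% power, again with about 50% between subjects.
- **Synergy** (NIKA plus EMDR versus NIKA only): a two-level model without a therapist level, with the statement "estimating 80% variance to occur between subjects, we will have 68% power to detect effects of" d = 0.50. No group size is given, and nothing explains the move from 50% to 80%.

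Methods for additional analyses {20b} describes the synergy analysis as one "to compare dyads who have received both NIKA and EMDR, to dyads who have only received NIKA". Its outcomes are disrupted parenting, sensitive parenting, child PTSD symptoms, and "behavioral and emotional problems from the pre-test to the second post-test between these two groups". The first two are the outcomes that Phase 1 was powered on.

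**The concern.** With two time points, the between-subject share fixes the variance of the change score, so it drives power as strongly as the sample size does. Raising the share from 50% to 80% cuts the change-score variance by 60%. The article makes that change for one calculation only, although two of the outcomes were planned at 50% a few paragraphs earlier. If 80% were believed for the parenting measures, Phase 1 would have almost complete power rather than 86%. If 50% is believed, the synergy comparison has about half the stated power.

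Objectives {7} lists the synergy contrasts as directional secondary hypotheses, and the Discussion presents the additive effect as a distinctive feature of the trial. A reader who weighs a null synergy result against 68% power would give it more weight than it deserves if the Phase 1 share is nearer the truth.

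**Working it through.** **Inputs from Sample size {14}.** Effect sizes, variance shares and the Phase 1 and Phase 2 group sizes are as stated there. Those two phases use "two time points, and two-sided testing with a significance level of" 0.05. The level is not restated for the synergy comparison, so I assume it is the same.

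**Input that must be inferred.** The synergy group size is not stated. Phase 2 expects 80 mothers. If half come from the NIKA arm (40) and these split equally between EMDR and waitlist under the 1:1 allocation in Sequence generation {16a}, there are 20 per group.

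**Formula.** With two time points, the group-by-time test is equivalent to a two-sample t-test on change scores. In units of the total SD:

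- SD of change = √(2 × (1 − share))
- standard error = SD of change × √(1/n₁ + 1/n₂)
- noncentrality = d / standard error, with n₁ + n₂ − 2 degrees of freedom

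**Reproducing the plan's own figures**

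| Calculation | n per group | d | Share | SD of change | Noncentrality | Power | Stated |
|---|---|---|---|---|---|---|---|
| Phase 1 | 75 | 0.50 | 50% | 1.000 | 0.50/0.163 = 3.06 | 86.0% | 86% |
| Phase 2 | 40 | 0.60 | 50% | 1.000 | 0.60/0.224 = 2.68 | 75.5% | 75% |
| Synergy | 20 | 0.50 | 80% | 0.632 | 0.50/0.200 = 2.50 | 68.3% | 68% |

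One formula returns all three figures. A simulation of the synergy case gave 68.2%.

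**Changing only the share in the synergy calculation (20 v 20, d = 0.50)**

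| Share | SD of change | Noncentrality | Power |
|---|---|---|---|
| 80% | 0.632 | 2.50 | 68.3% |
| 70% | 0.775 | 2.04 | 51% |
| 60% | 0.894 | 1.77 | 41% |
| 55% | 0.949 | 1.67 | 37% |
| 50% | 1.000 | 1.58 | 33.8% |

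Simulation at 50% gave 34.3%. At that share, 68% power would need d of about 0.50/0.632 = 0.79, or about 49 per group.

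**The reverse check.** Putting 80% into Phase 1 (75 v 75, d = 0.50) gives 99.8% power, not the stated 86%. The two shares cannot both describe the parenting outcomes.

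**Does the simpler model explain the change?** No. Adding the whole 5% therapist share to the subject level gives 55% at most, where power is 37%.

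**Sensitivity to the inferred group size**

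| Groups | Power at 80% | Power at 50% |
|---|---|---|
| 18 v 18 | 63% | 31% |
| 22 v 22 | 73% | 37% |
| 20 v 55 (all other NIKA dyads, 75 − 20) | 85% | 47% |
| 37 v 38 | 92% | 57% |
| 40 v 40 | 94% | 60% |

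Of the sizes tried, 20 v 20 is the one that matches 68% at an 80% share (19 per group gives 66.0%, 21 gives 70.5%). None reaches 68% at a 50% share.

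**The case against.** Several objections are fair and limit the point.

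- **The 68% is not a miscalculation.** It follows from the 80% disclosed in the same sentence. This stands; the fault lies in the input.
- **A journal article may leave the reason for a variance share to the full protocol.** This stands for the missing reason taken alone. It does not remove the conflict between two shares printed for the same parenting outcomes.
- **The 34% depends on a group size the article never gives.** This stands. It must be presented as conditional on 20 v 20. Read literally, the additional-analyses section could take in NIKA dyads without clinical symptoms (20 v 55, 47% at a 50% share). That reading does not reproduce 68%, and Objectives {7} confines the hypothesis to parents with PTSD symptoms.
- **The conflict covers only half of the outcomes.** This stands. The plan sets no 50% share for child PTSD symptoms or child behavioural and emotional problems.
- **The comparison is already framed as exploratory.** This is true of both the sample size and the additional-analyses sections, and it lowers the stakes.

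A reader might also infer that 80% is wrong and 50% right. The documents do not support that, because neither share is sourced. A reader might add that the synergy contrast runs over about 12 weeks rather than 6 and should therefore have a lower pre-post correlation. Nothing in the article says so, and the model used here has a single share whatever the interval, so I place no weight on it.

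**Conclusion.** For disrupted and sensitive parenting, the article uses two incompatible between-subject shares, and the stated synergy power depends on the more favourable one. Assuming 20 v 20, d = 0.50, two-sided 5% and a change-score comparison, power falls from 68% at an 80% share to 34% at the 50% used in Phase 1, with 41% and 51% at 60% and 70%. With 18 to 22 per group, the figure at 50% is 31% to 37%.

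The finding does not extend further. The planned N of 150 and the two primary power figures (86% and 75%) reproduce and are unaffected, so it would be wrong to infer that the trial is undersized for its primary hypotheses. It would also be wrong to call 34% the established power of the synergy comparison: it is the power under the plan's own Phase 1 assumption and an inferred group size, for the two parenting outcomes only.

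**What to change.** In the synergy paragraph of Sample size {14}:

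1. State the number per group (20 v 20, if that is what was used) and how it arises from the 80 Phase 2 mothers.
2. For disrupted and sensitive parenting, either use the Phase 1 share of 50% and restate the power as about 34%, or report 34–68% for shares of 50–80% and justify the 80%.
3. Say which outcomes the 80% was meant for, since the plan gives no other share for the child measures.
4. Keep the exploratory description and say that the result will be interpreted through its confidence interval.

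This changes wording only. It needs no extra participants and no change to the design or to the primary calculations. The one downside is a less favourable stated figure.
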